## Abstract

**Background:**

Lymphoceles are a common complication after pelvic lymphadenectomy in women with gynecologic malignancies. Although typically asymptomatic, lymphoceles can superinfect requiring medical or surgical intervention. A single center randomized controlled trial provided first evidence, that a collagen-fibrin patch (Tachosil®) is effective in the prevention of symptomatic lymphoceles after pelvic lymphadenectomy.

**Methods/Design:**

We will perform a multicentre, blinded, randomized, controlled trial comprising 140 women with gynecologic malignancies undergoing pelvic lymphadenectomy. Women will be randomly allocated to Tachosil® application or no application. Primary outcome is efficacy, defined as lymphocele CTCAE 4.03 grade ≥2 within four weeks after surgery. Secondary outcomes are asymptomatic lymphocele verified by ultrasound, medical or surgical intervention. Assuming a two-sided 5% significance level, a power of 80%, and a drop out rate of 10%, a sample size of 68 patients per group was calculated to detect a 66% absolute decrease in symptomatic lymphoceles.

**Discussion:**

We aim to provide further evidence for the efficacy of a collagen-fibrin patch in the prevention of symptomatic lymphoceles in women with gynecological malignancies undergoing pelvic lymphadenectomy.

**Trial registration:**

This study is registered at ClinicalTrials.gov (NCT01470677, protocol ID: TACHO-1). This study is registered at the EudraCT database (EudraCT number: 2011-003115-34).

## Background

Women with gynecologic malignancies such as cervical and endometrial cancer routinely undergo pelvic lymphadenectomy based on tumor characteristics assessed prior to or during surgery. Pelvic lymphadenectomy may be performed by open surgery or laparoscopy [1–4]. The rate of intraoperative complications during and after laparoscopic and open pelvic lymph node dissection is generally low, but has potential long-term consequences such as lower extremity lymph edema, nerve injury, and chronic pain. O’Hanian et al., for example, describe an intraoperative complication rate of 7% in a series of 30 patients with pelvic and paraaortic lymphadenectomy [1]. In a series of 257 women with cervical cancer undergoing laparoscopically assisted radical trachelectomy and pelvic lymphadenectomy, Marchiole et al. describe 11 (4%) intraoperative complications with 5 (2%) of these attributable to lymphadenectomy, i.e. vascular and ureteral injury [2]. Xu et al. performed laparoscopic pelvic lymphadenectomies in 313 patients with cervical cancer, 143 of which also underwent paraaortic lymphadenectomy and report 7 (2%) cases of intraoperative complications possibly related to lymphadenectomy [3]. Postoperative complications during and after pelvic lymphadenectomy include local abscess, bleeding, lymphocele, and chronic lymphedema of the lower extremities, which has an incidence of 1 to 2% [2, 3]. The rate of complications does not seem to differ significantly in women undergoing open or laparoscopic lymphadenectomy based on the available literature [1–6].

In the present trial, we will focus on pelvic lymphoceles, one of the most common complications of pelvic lymphadenectomy. Simonato et al. described a rate of 19/30 (63%) of sonographically detected lymphoceles in men undergoing pelvic extraperitoneal lymphadenectomy for prostate cancer [4]. In this trial, 4/19 men with lymphoceles were symptomatic and required medical interventions. In women with cervical cancer, asymptomatic lymphoceles detected by ultrasound have been noted in up to 11% of women after pelvic lymphadenectomy [1, 3, 5]. In 2% of women, clinical symptoms will require a therapeutic intervention [6].

Tachosil® is a fibrin-collagen coated patch and has been licensed in 2004 in Europe for surgical use in humans to support surgical hemostatic interventions. The efficacy and safety of Tachosil® has been demonstrated in liver resection, pulmonary lobectomy, and kidney tumor resection trials [7–9]. In men, but not in women, it has been demonstrated that the application of a collagen-fibrin patch to the lymphadenectomy surgery site may prevent a significant proportion of lymphoceles. In a randomized trial, Simonato et al. found that the pelvic application of two Tachosil® patches to the obturator fossa and the femoral canal was sufficient to significantly reduce the rate of sonographically detected lymphoceles within 4 weeks after surgery from 19/30 to 5/30 cases (p = 0.001) as well as the mean drainage volume from 190 to 64 ml. Percutaneous puncture of a symptomatic lymphocele was necessary in 1/30 individuals in the intervention group compared to 4/30 individuals in the control group [4]. In women with gynecological malignancies a single center randomized controlled trial has found, that Tachosil® seems effective to reduce the rate of lymphoceles after pelvic lymphadenectomy [5]. 7/30 (23.3%) women in the treatment group compared to 9/28 (57.7%) women in the control group developed asymptomatic lymphoceles (p < 0.05) [5]. No significant differences between the two groups were observed in the development of symptomatic lymphoceles or the rate of interventions [5]. This may be attributable to the small sample size of this study. As symptomatic lymphoceles are more relevant for the patient, it seems clinically more important to evaluate the impact of Tachosil® on the rate of symptomatic lymphoceles after pelvic lymphadenectomy.

Symptomatic lymphoceles are defined by the CTCAE 4.03 grading system as lymphoceles grade ≥2. This includes all lymphoceles needing medical intervention. Thus this definition comprises, lymphoceles with the presence of localized pelvic pain, pelvic abscess, fever, and/or leg edema in the presence of a sonographically verified pelvic lymphocele.

In summary, the data available in the literature demonstrate that pelvic lymphoceles occur in 11 to 63% of individuals undergoing pelvic lymphadenectomy. Symptomatic lymphoceles seem to occur in about 32% of patients undergoing pelvic lymphadenectomy. Intraoperative application of a collagen-fibrin patch may reduce the number of lymphoceles, mean drainage volume, and the necessity of medical interventions such as percutaneous puncture.

Therefore, we intend to perform a multi center randomized clinical trial assessing the efficacy of a collagen-fibrin patch for preventing symptomatic lymphoceles in women undergoing pelvic lymphadenectomy for gynecologic malignancies, ie cervical and endometrial cancer. We hypothesize that, based on the data of Simonato et al. and Tinelli et al., the application of a collagen-fibrin patch (Tachosil®) will reduce the number of symptomatic pelvic lymphoceles by at least 66%.

## Methods/Design

### Aim of the study

Primary outcome variable:

2.1.1. To evaluate the incidence of symptomatic pelvic lymphoceles defined by CTCAE 4.03 grade ≥2 within 4 weeks after surgery in women undergoing open or laparoscopic pelvic lymphadenectomy for cervical and endometrial cancer with and without the application of Tachosil® during surgery.

Secondary outcome variables:

2.1.2 To evaluate the incidence of sonographically detected pelvic lymphoceles of at least 2 cm in the largest diameter 4 weeks after surgery in women undergoing open or laparoscopic pelvic lymphadenectomy for cervical and endometrial cancer with and without the application of Tachosil® during surgery.

2.1.3. To evaluate the rate and type of medical interventions for clinically symptomatic pelvic lymphoceles such as analgesics and/or lymphocele puncture and drainage.

2.1.4. To evaluate the rate of total and symptomatic lymphoceles between the three centers.

2.1.5. To evaluate the rate of total and symptomatic lymphoceles between cervical and endometrial cancer patients.

2.1.6. To evaluate the rate of total and symptomatic lymphoceles between the surgical device used for pelvic lymphadenectomy.

2.1.7. To evaluate the rate of total and symptomatic lymphoceles between patients with and without lymph node metastases.

2.1.8. To evaluate the risk for total and symptomatic lymphoceles depending on the total number of pelvic lymph nodes removed.

2.1.9. To evaluate the rate of total and symptomatic lymphoceles between patients with open and laparoscopic pelvic lymphadenectomy.

### Study hypothesis

We hypothesize that the intraoperative application of two collagen-fibrin patches (Tachosil®) to the obturator fossa and the femoral canal will reduce the number of symptomatic pelvic lymphoceles by at least 66% (primary study end point).

### Study design

Prospective randomized clinical intervention trial of 140 women undergoing open or laparoscopic pelvic lymphadenectomy for cervical or endometrial cancer. Randomization will be by a computerized randomization list. Women will be centrally randomized by the principal investigator (CT). Allocation will be communicated by telephone after informed consent has been obtained and after lymphadenectomy has been completed. This is a single-blinded study, ie patients, but not surgeons, will be blinded to the treatment allocation. Outcome assessment will not be performed by the surgeon, who has performed the lymphadenectomy. Outcome assessors will be blinded to the treatment allocation.

### Inclusion criteria

Women undergoing open or laparoscopic surgery for cervical or endometrial cancer.Age between 18 and 70 yrs.Informed consent.

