### Statistical analysis

A power calculation demonstrated that, with a sample size of 70 per group, a two-arm study has a power of 80% to detect a 66% absolute difference in treatment efficacy at a significance level of 0.05 regarding the primary outcome parameter, ie symptomatic lymphoceles CTCAE 4.03 grade ≥2. This calculation was based on published data by Tinelli et al. observing a rate of 32% of symptomatic lymphoceles in the placebo group and 10% in the Tachosil® group [5]. Assuming a 10% drop out-rate, 140 women will be randomized. The chi-square test will used for comparisons of frequencies and cross-tabulations. One Way ANOVA on ranks will be used on means. Descriptive statistics (means, standard deviations, and ranges) will be used for demographic data. Bonferroni’s correction will be used for multiple comparisons of secondary outcomes.

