The value of Tachosil® in the prevention of lymphoceles after pelvic lymphadenectomy in women has already been studied in two clinical trials [5, 13]. In a retrospective matched case–control study, a cohort of 26 patients receiving Tachosil® after laparoscopic pelvic lymphadenectomy was compared to a historical cohort of 29 women without Tachosil® after laparoscopic pelvic lymphadenectomy. The study described a significant difference in the prevalence of total lymphoceles (19.2% of patients in the Tachosil® group vs. 51.7% in the historical control group) and a non-significant difference of symptomatic lymphoceles (7.6% of patients in the Tachosil® group vs. 17.2% in the historical control group). Of note, this was not a prospective trial with a limited number of patients [13]. The second study was a prospective randomized controlled trial comprising 58 women with endometrial cancer after undergoing pelvic lymphadenectomy with or without Tachosil® [5]. This trial observed, that Tachosil® seems effective to reduce the rate of lymphoceles after pelvic lymphadenectomy [5]. 7/30 (23.3%) women in the treatment group compared to 9/28 (57.7%) women in the control group developed asymptomatic lymphoceles (p < 0.05) [5]. No significant differences between the two groups were observed in the development of symptomatic lymphoceles or the rate of interventions [5]. This may be attributable to the small sample size of this study.

As symptomatic lymphoceles are more relevant for the patient, it seems clinically more important to evaluate the impact of Tachosil® on the rate of symptomatic lymphoceles after pelvic lymphadenectomy. Therefore, we intend to perform a multi center randomized clinical trial assessing the efficacy of a collagen-fibrin patch for preventing symptomatic lymphoceles in women undergoing pelvic lymphadenectomy for gynecologic malignancies, ie cervical and endometrial cancer. We hypothesize that based on the data of *Simonato et al.* and *Tinelli et al.*, the application of a collagen-fibrin patch (Tachosil®) will reduce the number of symptomatic pelvic lymphoceles by at least 66%.

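### The 80% power rests on rates from an endometrial-only trial, although cervical cancer is also enrolled; it is not supported for the mixed population and depends on an unstated cancer mix

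*Protocol article*

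**What the plan says.** The Inclusion criteria admit "Women undergoing open or laparoscopic surgery for cervical or endometrial cancer". Study design and Study population repeat both cancers, and no expected share of either is given. The Statistical analysis section rests the power statement on reference [5], "observing a rate of 32% of symptomatic lymphoceles in the placebo group and 10% in the Tachosil® group". The abstract gives the other inputs: "Assuming a two-sided 5% significance level, a power of 80%, and a drop out rate of 10"%. The Discussion describes reference [5] as a "prospective randomized controlled trial comprising 58 women with endometrial cancer after undergoing pelvic lymphadenectomy with or without Tachosil® [5"].

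The Background nevertheless concludes, without limiting it to one cancer, that "Symptomatic lymphoceles seem to occur in about 32% of patients undergoing pelvic lymphadenectomy", and the Discussion repeats this. Earlier the Background says "In women with cervical cancer, asymptomatic lymphoceles detected by ultrasound have been noted in up to 11% of women after pelvic lymphadenectomy [1, 3, 5"], followed by "In 2% of women, clinical symptoms will require a therapeutic intervention [6"]. The Discussion also reports a retrospective comparison in women with 17.2% symptomatic lymphoceles among controls and 7.6% with the patch. The planned test for frequencies is a chi-square test. Cancer type appears only as a secondary comparison (Aim of the study, 2.1.5).

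**The concern.** A planning rate observed in one cancer is applied to a trial of two, with no argument that it carries over and no sensitivity range. It is also the highest symptomatic rate the article quotes for women. If the control rate in the enrolled mix is lower, the number of events falls and so does the power of 140 women. A null result could then reflect too few events rather than an ineffective patch, and a reader relying on the stated 80% would misjudge it. The weakness lies in the planning assumption, not in the decision to enrol both cancers.

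**Working it through.** **1. The plan's own figure.** Inputs: control 32%, patch 10% (Statistical analysis); two-sided 5%, power 80%, drop-out 10% (abstract). The mean rate is 0.21.

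n = [1.960·√(2·0.21·0.79) + 0.842·√(0.32·0.68 + 0.10·0.90)]² / 0.22² = 52.6, so 53 per arm.

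With continuity correction: (52.6/4)·[1 + √(1 + 4/(52.6·0.22))]² = 61.4, so 62 per arm. Allowing for drop-out, 62/0.9 = 68.9, so 69 per arm. This agrees closely with the printed 68 (abstract) and 70 (Statistical analysis). The size therefore follows from 32% against 10%, and the question is whether those rates fit the population.

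**2. Power if cervical patients have a lower control rate.** Let f be the cervical share and r the cervical control rate of the primary endpoint. The article gives neither, so both are assumptions.

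- Pooled control rate: p₁ = 0.32(1 − f) + r·f
- Patch rate: p₂ = p₁·(10/32), which assumes the planned relative effect in both cancers
- Evaluable per arm: 70·0.9 = 63
- Power: the sum of binomial probabilities over all outcome pairs for which the uncorrected two-sided 5% chi-square test is significant

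Two illustrative values of r are used: 2%, and 13% (the sum 11% + 2% from the Background).

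| Cervical share f | r = 2%: p₁ vs p₂ | Power | r = 13%: p₁ vs p₂ | Power |
|---|---|---|---|---|
| 0 | 32.0% vs 10.0% | 88% | 32.0% vs 10.0% | 88% |
| 0.3 | 23.0% vs 7.2% | 71% | 26.3% vs 8.2% | 78% |
| 0.5 | 17.0% vs 5.3% | 57% | 22.5% vs 7.0% | 70% |
| 0.6 | 14.0% vs 4.4% | 48% | 20.6% vs 6.4% | 66% |

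Power first drops below 80% at f of about 0.17 (r = 2%) or 0.26 (r = 13%). In both cases the pooled control rate is then about 27%: 0.32·0.83 + 0.02·0.17 = 0.269, and 0.32·0.74 + 0.13·0.26 = 0.271. If all 70 per arm were evaluable, the shares would be about 0.25 and 0.39. At a 10% cervical share with r = 2% and 63 per arm, power stays at about 82% by the usual normal formula.

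**3. The other symptomatic rates in women.** At 17.2% against 7.6%, 63 per arm give about 37% power. Part of this is a weaker effect (7.6/17.2 = 0.44, against 10/32 = 0.31). With 17.2% and the planned relative effect, power is about 56% by the normal formula.

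**The case against.** A reader might infer more than the article supports, and the case against the stronger readings is good.

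- **That 80% power is lost.** This is not shown. The calculation has reserve: 88% with 63 per arm, and 91% with 70, if no cervical patients enter. The loss needs a cervical share above roughly 17% to 39%, depending on the assumed rate and drop-out, and no share is stated.
- **That the article gives cervical rates of 2% to 13% for the endpoint.** It does not. The 11% is asymptomatic and found by ultrasound, and its citations include reference [5], the endometrial trial itself. The 2% sentence does not repeat the cancer type, and it counts therapeutic interventions, which are not shown to equal CTCAE grade 2 or higher. Their sum is no upper bound.
- **That cancer type is strongly prognostic.** The rates come from different studies with different endpoints. The Discussion attributes the variation to follow-up time, small studies, extent of surgery, energy source and surgical approach. Cancer type is not among these, and objective 2.1.5 leaves it open.
- **That the inclusion criterion is wrong, or that randomisation is unstratified.** Enrolling both cancers matches the stated aim. The article mentions a computerised list without saying whether it has strata, and a condensed article may leave that out.

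There is also a doubt about the 32% that has nothing to do with cancer type. The Background and Discussion report 9/28 controls in reference [5] (9/28 = 32.1%, although printed as 57.7%) as asymptomatic lymphoceles.

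All of these limits stand. They do not remove the core: a rate from an endometrial-only trial is generalised and used for a mixed trial, while every other symptomatic rate quoted for women is lower.

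**Conclusion.** The concern holds as a conditional one. The stated 80% power is not supported for a cervical-plus-endometrial population, and the article supplies neither of the two quantities needed to support it. Under the planned relative effect with 63 evaluable per arm, 80% requires a pooled control rate of about 27% or more. At half cervical, power would be about 57% to 70% for assumed cervical rates of 2% to 13%. These figures rest on three assumptions: 32% is correct for endometrial cancer, the 10/32 ratio applies in both cancers, and the cervical rate lies in the range shown. They illustrate sensitivity and do not estimate this trial's power.

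**What to change.** 1. In Statistical analysis and the abstract, state the expected cervical/endometrial mix and report the power of 140 women over a stated range of pooled control rates, labelled as assumptions, instead of a single 80%.
2. In Background and Discussion, attribute the 32% to the endometrial trial [5] only, after checking that it is a symptomatic rate, given the 9/28 reported there as asymptomatic.
3. Replace the plain chi-square test for the primary comparison with one stratified by cancer type, for example Cochran-Mantel-Haenszel. Cancer type is known before inclusion. In simulation under the rates assumed above, this added about 1 to 4 percentage points of power and kept the type I error at 5%. Stratifying the randomisation list as well is optional.

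The cost is a less favourable power statement and one stratification term in the analysis. No additional patients or data are required.

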### Exclusion criteria

Women with previously diagnosed lymph edema.Known disease of the lymphatic system.Immunocompromised women such as those with an immunosuppressive medication or a known disease of the immune system.

### Treatment

All women will undergo open or laparoscopic surgery. Within this procedure, as deemed appropriate by the surgeon, women will undergo pelvic lymphadenectomy. The procedure will be performed as follows:The peritoneum will be incised parallel to the iliac vessels. Then, the iliac vessels will be screened for the presence of bulky lymph nodes. If a lymph node debulking is performed, no patch will be applied. In women who undergo routine pelvic lymphadenectomy, lymph node tissue will be removed from the external iliac vessels, the obturator fossa, the interiliac region, and the common iliac region after identification and appropriate preparation of surgical landmarks, ie iliac vessels, femoral canal, chorda, and obturator nerve. At the end of the procedure, hemostasis will be checked. A Tachosil® patch of 4.8x4.8 cm will be attached to the obturator fossa and a Tachosil® patch of 4.8x4.8 cm will be attached to the femoral canal of each side of surgery in the intervention group (Figures 1, 2 and 3). In the control group, no Tachosil® patch will be used. No specific drainage of the retroperitoneum will be performed. The study team members [name], [name], and [name], experienced in open and laparoscopic pelvic lymph node dissection, will perform all surgical procedures. In order to ensure adequate application of the Tachosil® patch by laparoscopy, all surgeons will perform at least two laparoscopic training operations during which they roll the Tachosil® patch around a laparoscopic instrument, move it through a 10 mm trocar into the abdomen, and flatten it out.

**Figure 1 Fig1:**
[figure not shown]
**Right pelvic side wall after systematic pelvic lymphadenectomy.** 1 = Right external iliac artery. 2 = Right internal iliac artery, 3 = Right obturator nerve.

**Figure 2 Fig2:**
[figure not shown]
**Tachosil® is applied with a wet glove and sponge and compression for 30–60 seconds.** Thereafter glove and sponge are removed.

**Figure 3 Fig3:**
[figure not shown]
**Placement of the first Tachosil patch in the right obturator fossa.** 1 = Right external iliac artery. 2 = Right internal iliac artery.

Patients have to agree to participate in the study and sign informed consent at least one day before surgery. If patients are eligible and agreed to participate, they are included in consecutive order. Patients receive an envelope according to their inclusion number in which allocation is documented. This envelope accompanies the patient into the operating room. A nurse opens the envelope not before pelvic lymphadenectomy and hemostasis have been completely finished. According to the treatment group the patient is allocated, the surgeon now has to apply either two Tachosil® patches in the intervention group or no Tachosil® in the control group. Therefore, the surgeon cannot influence the extent of the lymphadenectomy, as he is not aware of the patient’s allocation until the end of the lymphadenectomy.

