## Conclusion

Despite being one of the major complications of lymphadenectomy, little is known about the prevention of lymphoceles. One prospective controlled trial comprising 58 women already evaluated the preventative effect of Tachosil® in the prevalence of lymphoceles (5). As this trial was not adequately powered to detect differences between symptomatic lymphoceles, we designed the present open, randomized, controlled trial.

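### The protocol gives two unreconciled allocation mechanisms, a central telephone release and an envelope the patient receives, and its Conclusion calls a blinded trial open

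*Protocol article*

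**What the plan says.** The protocol article describes allocation in two places.

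**Study design.** A computer-generated list is used ("Randomization will be by a computerized randomization list"). The person who randomizes is named by role: "Women will be centrally randomized by the principal investigator". The release is then described: "Allocation will be communicated by telephone after informed consent has been obtained and after lymphadenectomy has been completed". On blinding, the section says that "patients, but not surgeons, will be blinded to the treatment allocation", and that outcome assessors are blinded too.

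**Treatment** (the text after the caption of Figure 3). Women consent at least a day before surgery and are included consecutively. Then: "Patients receive an envelope according to their inclusion number in which allocation is documented". The next step is: "This envelope accompanies the patient into the operating room". A nurse opens it only when lymphadenectomy and hemostasis are finished. The surgeon then learns whether to apply the patches.

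The Abstract calls the trial blinded. The Follow-up section requires ultrasound examiners who did not take part in the operation and do not know the allocation. The Conclusion, however, says: "we designed the present open, randomized, controlled trial".

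**The concern.** An allocation procedure should tell each site one thing: who holds the assignment, and how it reaches the operating team. Here a site could follow either section and claim to comply. With three sites (Study population), different routes could run side by side without anyone departing from the protocol.

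The routes do not carry the same risk. Under the telephone route, nothing showing the assignment need exist near the patient or the surgical team until the call. Under the envelope route, a document holding the assignment exists before dissection and is received by the woman herself.

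Two safeguards are involved. The first is the Treatment section's argument that the surgeon cannot adapt the extent of lymphadenectomy, because he does not know the allocation until it is finished. The second is patient blinding. The Background section counts localized pelvic pain, with a lymphocele verified by ultrasound, among the symptomatic presentations that make up the primary endpoint. Use of analgesics is part of a secondary outcome. Both can respond to what the patient believes she received.

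**Working it through.** No arithmetic applies. The sample size and event rates do not depend on how the allocation is released. The check is a comparison of the sections.

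| Element | Study design | Treatment |
|---|---|---|
| Source of assignment | Computerized list; central randomization by the principal investigator | Envelope matched to inclusion number |
| Where the assignment is before dissection | Held centrally | On paper, received by the patient and taken to theatre with her |
| Who releases it | Central caller | Nurse in theatre |
| How | Telephone | Opening the envelope |
| When | After consent and after lymphadenectomy | After lymphadenectomy and hemostasis |
| Mention of the other route | None | None |

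**Step 1: can both be the operating procedure?** If the envelope already holds the assignment, the call has nothing to communicate. If the call delivers the assignment, the envelope has no purpose. One could suppose that the list is drawn up centrally and then distributed in envelopes. That would fit central randomization, but it leaves the telephone sentence unexplained. One could suppose that envelopes are a backup, or that sites differ. The text says neither.

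**Step 2: what do the routes share?** Both disclose only after the dissection. The envelope text adds that hemostasis must also be finished, which the telephone text does not say. The planned timing is therefore essentially consistent. What differs is the mechanism and who has custody.

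**Step 3: does the difference in custody matter here?** The envelope travels into theatre with the woman, so it exists before dissection starts. It is said to be received by patients, whom Study design says are blinded. Symptoms alone do not make an event, because a lymphocele must be seen on ultrasound by a blinded examiner. Among women with such a lymphocele, though, reported pain can decide whether it counts as symptomatic. Patient blinding therefore bears on the primary endpoint.

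**Step 4: are the blinding labels consistent?** *Blinded* in the Abstract and *single-blinded* with blinded assessors in Study design are compatible. *Open* in the Conclusion is not compatible with either, or with Follow-up.

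**The case against.** The best defence is that the safeguard that matters most, disclosure only after dissection, is stated in both places. That is correct, and it limits the point to mechanism and custody. It does not remove the point, because the sections still name different custodians and different release steps.

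It can also be said that a journal article condenses the full protocol. That covers details left out, such as whether envelopes are sealed or opaque, and nothing here rests on those. It does not cover two stated procedures that cannot both be the operating one.

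Several stronger readings are tempting, and the documents do not support them:

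- **The envelope is handed over at inclusion, or is on the ward before surgery.** The text ties the envelope to the inclusion number and sends it to theatre with the patient. It gives no time or place of hand-over.
- **Patients or surgeons will know the allocation early.** A nurse opens the envelope, which implies that it is closed until then. The text creates an opportunity; it does not show foreknowledge.
- **The principal investigator should not hold the list.** The principal investigators have access to study data, but outcome assessors are separately required to be blinded. An independent list-holder is a reasonable preference, but its absence is not a contradiction in this document.
- **The type I error is inflated by a stated amount.** The documents give nothing on how far foreknowledge would shift risk between the arms, so any such figure would only restate the assumed shift.

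The word *open* may be a slip, since the operational sections are explicit. It still needs correcting.

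**Conclusion.** The point holds as an internal inconsistency that should be fixed. Two allocation mechanisms are specified, nothing reconciles them, and one of them gives a blinded patient custody of her own assignment before dissection. The Conclusion's description of the trial as open contradicts Study design and Follow-up.

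The scope is the allocation of all 140 women at three sites. No numerical size can be given, and no figure in the plan changes. The conclusion rests on the wording of the two sections and assumes only that each is meant as the operating procedure, since neither is marked as an alternative. It does not rest on any breach having occurred. Because both sections delay disclosure until after lymphadenectomy, the matter falls short of a defect that would by itself invalidate the comparison.

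**What to change.** State one procedure for all three sites:

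1. Keep the central telephone release already described in Study design. Specify that the call is made only after lymphadenectomy and hemostasis are complete, taking the hemostasis condition over from the Treatment text.
2. Delete the patient-received envelope from the Treatment section. If envelopes are kept instead, hold them closed in theatre, never give them to the patient, and remove the telephone sentence or say which route is the backup.
3. In the Conclusion, replace *open* with a description that matches the rest of the document: patient- and assessor-blinded, surgeon unblinded.

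The cost is a short amendment and one instruction to the sites. The telephone route is already part of the plan, so no extra patients, visits or analyses are needed, and the sample size is unaffected.
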